### Safety monitoring

Possible adverse events (AEs) resulting from moxibustion include blisters, redness, itching, and burns. All unexpected and unintended responses will be reported as AEs by the researcher at every visit. AEs will be carefully recorded in the CRF by the corresponding research staff.

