## Abstract

**Background:**

Conventional moxibustion is a representative non-drug intervention in traditional Chinese medicine, and it has been reported to produce encouraging results and benefits in relieving symptoms and improving the quality of life for patients with knee osteoarthritis (KOA) in previous clinical trials and systematic reviews. Given that increasing concerns on the safety of generated smoke from conventional moxibustion have received much attention, smoke-free moxibustion is regarded as a potential alternative. However, whether smoke-free moxibustion would display a similar efficacy to that of conventional moxibustion still remains unclear. Therefore, this randomized controlled trial attempts to investigate the difference of efficacy between conventional moxibustion and smoke-free moxibustion in patients with KOA.

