## Background

Knee osteoarthritis (KOA) is the most common form of arthritis and is a major cause of disability and limitation of activity, especially in elderly patients [1]. It is characterized by pain and functional limitations, leading to a reduction in quality of life [2]. Osteoarthritis of the knee makes a significant impact on society, with more than 20 million Americans and 35 to 40 million Europeans developing this condition in their lifetime [3, 4]. Some recent international guidelines advocate non-pharmacological care for patients with knee pain [5–7]. As a representative non-drug intervention in traditional Chinese medicine (TCM) and a form of acupuncture [8–10], moxibustion has been reported to produce encouraging results and benefits in relieving symptoms and improving the quality of life for patients with KOA in many studies, including clinical trials and systematic reviews [11–15].

The mechanism of moxibustion is mainly related to its thermal effects, radiation effects, the pharmacological activity of moxa, and its combustion products (volatile oil, brown tar-like substances, and moxa smoke). Moxa smoke is a primary combustion product of moxibustion, and its potential effect on the health and environment may be controversial [16]. It was reported that moxa smoke has antibacterial and antiviral effects effective in treating various conditions including wound infections, vaginal itching, uterine prolapse, anal fistulas, common warts, and so forth [17–22]. However, some studies demonstrated that high levels of monoaromatic hydrocarbons, formaldehyde, and polycyclic aromatic hydrocarbons in the moxibustion room may have adverse effects on human health [23–25]. Epidemiological investigation also showed that the moxa smoke induced a variety of undesirable reactions such as dry throat, dry eye, and coughing [26]. Furthermore, with their increased environmental awareness, people have started to question the safety of the smoke produced by burning moxa [27–29]. Because of concerns as to the potential toxicity of the smoke, many acupuncturists prefer to use a smoke purification device to remove moxa smoke during the moxibustion treatment, but few studies have reported the difference of clinical efficacy between conventional moxibustion and smoke-free moxibustion (moxibustion using the smoke-removing device).

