**Fig. 1 Fig1:**
[figure not shown]
Flowchart of the study process. Participants with a diagnosis of KOA will be recruited from seven centers. All project general practitioners (*GPs*) were trained for 1 day. The trial period will consist of 12 sessions of moxibustion treatment over a period of 4 weeks. The treatment frequency will be three sessions per week, and there will be a 2-month follow-up period. The outcomes will be measured at every visit

**Table 1 Tab1:** Study design schedule

Period	Inclusion	Treatment		Follow-up	
	Baseline	First assessment	Second assessment	Third assessment	Fourth assessment
	0 week	2 weeks after inclusion	4 weeks after inclusion	8 weeks after inclusion	12 weeks after inclusion
Inclusion confirmed	√				
Informed consent	√				
Randomization and blinding	√				
Sociodemographic characteristics	√				
Disease history	√		√		
Treatment history	√		√		
Comorbidity	√		√	√	√
Current treatment	√		√	√	√
Outcomes					
WOMAC	√	√	√	√	√
VAS	√	√	√	√	√
PGA		√	√	√	√
Trial evaluation					
Outcome analysis					√
Adverse event			√		
Causes of dropout			√		
Safety analysis			√		
Compliance analysis			√		

*WOMAC* Western Ontario and McMaster Universities Osteoarthritis Index, *VAS* visual analog scale, *PGA* Patient Global Assessment

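### The adverse-event wording is ambiguous about known reactions and names no smoke symptom, although smoke is the only planned difference between the arms; its timing also differs from Table 1

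*Protocol article*

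**What the plan says.** The Safety monitoring section consists of three sentences:

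1. "Possible adverse events (AEs) resulting from moxibustion include blisters, redness, itching, and burns".
2. "All unexpected and unintended responses will be reported as AEs by the researcher at every visit".
3. "AEs will be carefully recorded in the CRF by the corresponding research staff".

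The Background reports epidemiological evidence that "the moxa smoke induced a variety of undesirable reactions such as dry throat, dry eye, and coughing". It explains the interest in smoke removal in the same terms: "Because of concerns as to the potential toxicity of the smoke, many acupuncturists prefer to use a smoke purification device". The abstract agrees, noting that "increasing concerns on the safety of generated smoke from conventional moxibustion have received much attention".

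The section on the smoke-free group says that, apart from the purification device, acupoints and other interventions are to be the same in both groups. The Discussion adds that the same kind of moxa is used so that smoke is what differs.

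In Table 1 the row "Adverse event" carries one tick, which appears to fall under the 4-week assessment. The WOMAC row carries five ticks: baseline and weeks 2, 4, 8 and 12.

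**The concern.** The events that could plausibly differ between these arms are those caused by smoke. The article names them in its Background, but its safety section names only skin reactions, which have no planned reason to differ because the acupoints and the rest of the treatment are the same.

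The second safety sentence joins two conditions, unexpected and unintended. A reaction already described in the article is arguably expected, so staff at seven centres could reasonably disagree on whether to report it.

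The Discussion says the trial will help in choosing a form of moxibustion for practice, and Table 1 schedules a safety analysis. A reader will therefore look at cough and eye or throat irritation by arm. If those counts depend on what was volunteered and how each centre read the rule, a difference or its absence will be hard to interpret.

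**Working it through.** No figure in the article depends on this point, so the check is a comparison of text.

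**Step 1. Apply the three safety sentences to each kind of event.**

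| Event | Named in sentence 1? | Sentence 2, read literally | Sentences 1 and 3 together |
|---|---|---|---|
| Burns, blisters, redness, itching | Yes | Unintended, but listed as possible and so arguably expected: may fail | Called AEs, and AEs go on the CRF: recorded |
| Cough, dry throat, dry eye | No, but the list is open | Unintended; arguably expected, since the Background describes them: may fail | Recorded only if someone first classes them as AEs |

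For the skin reactions, the section read as a whole favours recording. For the smoke symptoms, the stated route is sentence 2, and that sentence carries the restriction.

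**Step 2. See whether the literal rule treats the arms alike.** A cough is a foreseeable reaction in the room with smoke and less foreseeable where smoke is removed. The same symptom could therefore count as expected in the conventional arm and unexpected in the smoke-free arm. Staff who worry about smoke might instead note more symptoms in the conventional arm. The direction cannot be told from the documents.

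**Step 3. See who could report differently.** The Blinding section lists participants, outcome assessors, the data manager and the statistician as blinded. Treating practitioners are not listed; they fit the device, and the groups use separate rooms. The safety section assigns reporting to a researcher and recording to research staff without saying whether either is blinded.

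**Step 4. Look for another route to these symptoms.** The outcomes are WOMAC, pain VAS and Patient Global Assessment, none of which is described as covering them. The daily diary covers knee pain attacks, what accompanies them, and medication. The article therefore describes no prompt for smoke symptoms.

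**Step 5. What uneven capture does.** Let p1 and p2 be the true risks in the conventional and smoke-free arms, and c1 and c2 the fractions of events captured. The expected observed risk difference is

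c1·p1 − c2·p2.

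- If c1 = c2 = c, this is c·(p1 − p2): the difference shrinks but keeps its sign.
- If p1 = p2 = p and c1 ≠ c2, it is p·(c1 − c2): a difference appears where none exists.

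The documents give none of the four quantities, so no numerical size follows. A power figure for 69 per arm would be purely hypothetical and is not offered.

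**Step 6. Timing.** There are four assessments after baseline (weeks 2, 4, 8 and 12). The text has AEs reported at each visit; Table 1, as printed, has one tick. If visits mean these assessments, the table shows 1 of 4.

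**The case against.** The case on the other side is substantial, and much of it stands.

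- **Burns and blisters.** A reader might infer that they fall outside the rule. The documents do not support that: the first sentence calls them adverse events and the third records adverse events without limit. Only the second sentence taken alone excludes them. What remains is ambiguity.
- **Smoke symptoms.** A reader might infer that they are not collected, or that a low count would be an artefact of the rule. That also goes too far. The list is open, and a cough is plainly an unintended response that staff could report. The symptoms are unprompted, not excluded.
- **Aim.** The stated aim is to compare efficacy; smoke safety is motivation. The trial cannot be faulted for lacking a formal safety endpoint. It can still be asked to collect its planned safety data evenly.
- **Unseen CRF.** A condensed article may omit a symptom checklist that exists. If the CRF already prompts for these symptoms, only the wording and the table need attention.
- **Table 1.** The trial-evaluation rows may mark evaluation points and not collection times: outcome analysis is ticked only at week 12 although outcomes are collected at five time points, and causes of dropout share the single week-4 tick. A merged cell may also have been lost in conversion. So this is a discrepancy to clarify, not proof that AEs are collected once.
- **Lateness.** Recruitment ran from June 2016 and was expected to end in May 2017; the article appeared on 24 April 2017. A change at that stage would reach few new participants and would create two ways of ascertaining events.

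**Conclusion.** The point holds as a modest one about wording and ascertainment. The reporting sentence, read literally, lets known reactions go unreported. The named events omit the symptoms that the article itself ties to the only planned difference between the arms. As described, reporting is unprompted in a setting where treating staff know the allocation. The schedule table and the text need reconciling on timing.

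The size cannot be quantified from the documents. The sample size of 138 and the efficacy analysis are untouched; what is weakened is any between-arm reading of smoke-related events. The documents do not support the broader conclusion that the trial can say nothing about smoke harm.

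This rests on two assumptions: that the CRF does not already prompt for these symptoms, and that the person recording AEs may know the allocation. If either fails, the concern about uneven capture shrinks, but the wording and the Table 1 discrepancy remain.

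**What to change.** 1. In Safety monitoring, define reportable events as all untoward events, whether expected or not.
2. If the CRF does not already do so, ask about cough, dry throat and dry or irritated eyes, alongside the listed skin reactions, with the same wording in both arms at each scheduled assessment.
3. Reconcile the adverse-event row of Table 1 with the text, and state whether its ticks mark collection or evaluation.
4. Summarise smoke-related events by arm descriptively, with a risk difference and 95% confidence interval, as a secondary safety result and not as a new endpoint on a level with efficacy.

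The cost is about one CRF page and a short amendment, with no extra visits. There are three downsides:

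- Solicited questions raise AE counts in both arms, so totals will not compare directly with trials that rely on spontaneous reports.
- Questions about smoke symptoms could hint at what differs between the groups, so they need neutral wording to protect participant blinding.
- If the change comes during recruitment, events before and after it must be reported separately.

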## Methods/design

### Design

This is a multicenter, randomized, single-blinded, parallel-group design clinical trial conforming to Consolidated Standards of Reporting Trials (CONSORT) and Standards for Reporting Interventions in Clinical Trials of Acupuncture (STRICTA) guidelines [30, 31]. A Standard Protocol Items: Recommendations for Interventional Trials (SPIRIT) checklist is provided in Additional file 1. A total of 138 eligible participants with KOA will be randomly allocated into two groups (moxibustion group or smoke-free moxibustion group) with a 1:1 allocation ratio. Eligible participants who meet the clinical criteria for KOA formulated by the American College of Rheumatology (ACR) will be enrolled in this trial [32]. Seven clinical research centers in China will participate in this trial: Central Hospital of ZiBo, Chengdu First People’s Hospital, Sichuan Second Hospital of TCM, Pi County People’s Hospital, Xinjin County TCM Hospital, Qionglai TCM Hospital, and Nanjing Hospital of TCM. The study period is 13 weeks, with a 1-week baseline period, 4-week treatment phase, and 8-week follow-up phase. After randomization, eligible participants will receive 12 sessions of moxibustion treatment over a period of 4 weeks. Patients will be assessed at the baseline visit, as well as at 2 weeks, 4 weeks, 8 weeks, and 12 weeks after allocation. The trial diagram demonstrates the procedures of the study (see Fig. 1). Table 1 outlines the measures used throughout this trial.

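### Table 1 schedules adverse events at week 4 only, while the safety text requires reporting at every visit; the two need reconciling

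*Protocol article*

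**What the plan says.** The Safety monitoring section gives the rule on timing: "All unexpected and unintended responses will be reported as AEs by the researcher at every visit". It adds that "AEs will be carefully recorded in the CRF by the corresponding research staff", with no limit on when.

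The Design section defines the visits: "Patients will be assessed at the baseline visit, as well as at 2 weeks, 4 weeks, 8 weeks, and 12 weeks after allocation". It also gives the phases: "The study period is 13 weeks, with a 1-week baseline period, 4-week treatment phase, and 8-week follow-up phase".

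Table 1 (Study design schedule) has a block labelled "Trial evaluation". In it, the rows "Adverse event", "Causes of dropout" and "Safety analysis" each carry one tick, at the second assessment (week 4). In the outcome block, WOMAC and VAS are ticked at all five time points and PGA at all four post-baseline ones.

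**The concern.** A site cannot follow both the safety text and the AE row of Table 1 as they stand. With seven centers, different sites could settle the conflict in different ways, and AE ascertainment would then differ between centers.

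The visits at issue matter for harms. A patient who stops before week 4, possibly because of a burn or blister, would not reach the only ticked AE entry. A harm from the last sessions that shows or persists after week 4 would have no scheduled entry, although the patient returns at weeks 8 and 12. The Background section presents concern about the safety of moxa smoke as a reason for the trial, so readers will look at its harm data even though the stated aim is efficacy.

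Reasons for dropout also bear on the efficacy analysis. The Analysis section plans multiple imputation, and the causes of withdrawal help a reader judge whether its assumptions are plausible.

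**Working it through.** The plan gives no figure to reproduce here. The check reads Table 1 row by row and sets it against the text.

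**Step 1. Is the table read correctly?** Each row was split into its five cells and matched to the five assessment columns. Rows whose timing is known or plain serve as alignment checks.

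| Row | Baseline | Wk 2 | Wk 4 | Wk 8 | Wk 12 |
|---|---|---|---|---|---|
| WOMAC (check) | x | x | x | x | x |
| PGA (check) | | x | x | x | x |
| Comorbidity (check) | x | | x | x | x |
| Outcome analysis (check) | | | | | x |
| Adverse event | | | x | | |
| Causes of dropout | | | x | | |
| Safety analysis | | | x | | |
| Compliance analysis | | | x | | |

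Every row gives five cells, and the check rows land where they should. An extraction fault in the AE row is therefore unlikely, though a merged cell in the original cannot be fully excluded. The comorbidity row also shows that the table marks follow-up collection where it is meant.

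**Step 2. Count AE occasions under each rule.**
- Safety text with the Design section: weeks 2, 4, 8 and 12, so 4 of 4 post-baseline assessments. If visits include the treatment sessions, there are more.
- Table 1: week 4 only, so 1 of 4.

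**Step 3. Time after the table's only AE tick.** Treatment lasts 4 weeks and follow-up 8, so 12 weeks run from allocation. 12 − 4 = 8 weeks follow the tick, and 8/12 = 67%. All of that time is after treatment has ended, so it measures follow-up without a scheduled AE entry, not the share of harms missed.

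**Step 4. Early leavers.** The anticipated dropout is 15% of 138: 0.15 × 138 = 20.7, about 21 patients over the whole study. At that rate, 21 is the ceiling on those who could leave before week 4. Dropout timing is not stated, so the number could lie anywhere from 0 to 21.

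**Step 5. The other two rows.** The every-visit rule names AEs only, so one tick for causes of dropout and one for safety analysis do not contradict it. They are awkward for a different reason. Withdrawal can happen at any time, and a single column does not fit that. A safety analysis at week 4 would come before the AEs that the text requires at weeks 8 and 12, whereas the outcome analysis is ticked at week 12.

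**The case against.** The strongest defense is that the rows in question sit in a block about evaluating the trial, not about collecting outcomes. In that block the outcome analysis is ticked only at week 12 although WOMAC is measured five times, and the compliance analysis only at week 4 although there are 12 sessions. A single tick there may mark when an item is summarized, not the only time it is collected. The article also condenses a fuller protocol, treatment manual and CRF, and nothing in it says that Table 1 overrides the text. Treatment ends at week 4, and the AEs listed (blisters, redness, itching, burns) are those resulting from moxibustion, so most may have appeared by then.

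Much of this stands. A reader might infer that the trial collects no harms at week 2, in follow-up or from early leavers, and that its harm rates are biased downward. The documents do not support that. The safety text requires AE reporting at every visit and entry in the CRF, so absent collection follows only if the table governs. Under-recording is a conditional risk, and any bias between arms is more conditional still. Nor can the 21 expected dropouts be counted as lost to AE recording: some may leave after week 4, with that entry already made. A cause of dropout may also be recorded when it occurs, whatever the table shows.

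The defense does not remove the point. The AE and dropout-cause rows are separate from the two analysis rows and read as data items. If they are summaries instead, a safety summary at week 4 still precedes AEs due at weeks 8 and 12. The daily diary does not close the gap either: it covers knee pain attacks, associated phenomena and medication, and is not described as an AE record.

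**Conclusion.** The contradiction holds: Table 1 shows AE collection at 1 of 4 post-baseline assessments, and the Safety monitoring text requires it at all 4. Its consequence is conditional. If sites or CRF pages follow the table, harms at week 2, in the 8 weeks of follow-up and among patients who leave before week 4 have no scheduled entry and could be under-recorded. If they follow the text, AE collection is complete and only the table is wrong. The documents do not show which applies.

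The placement of the dropout-cause and safety-analysis ticks is a separate scheduling weakness, not a breach of the every-visit rule. No count of missed events or affected patients can be given.

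The conclusion assumes that the extracted table matches the published one, which the aligned rows support. It leaves the primary endpoint intact. The correction should be made because it is cheap and protects the harm data.

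**What to change.** - Tick the adverse event row of Table 1 at weeks 2, 4, 8 and 12, and check that the CRF has an AE entry at each. If the CRF already has these, only the table needs correcting.
- Record the cause of dropout when it occurs, at any time up to week 12, and show this in the table as event-driven.
- Run the safety analysis after week 12 on all randomized patients, including those who stop early.

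Recording AEs at each of the 12 treatment sessions would go beyond reconciling the two rules and is not needed for this point.

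The cost is one corrected table, possibly a CRF page, and a little more recording at visits that already exist. The reported AE rate may rise somewhat because ascertainment is fuller. The Trial status section says recruitment is still under way, so the correction can reach patients who have not finished follow-up. For those who have, the report should state at which visits AEs were in fact recorded.

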## Discussion

Moxibustion is widely used in Asian countries to treat various disorders and is reported to be effective for relieving the pain and functional limitations of KOA [10, 12, 13]. Recent research has focused on the composition and the safety of moxa smoke, but few studies have considered the effect of moxibustion with removal of the moxa smoke [25]. The aim of this trial is to compare the effectiveness of conventional moxibustion and smoke-free moxibustion for patients with KOA.

In clinical application, the smoke-free moxa sticks have been used because of the concerns about moxa smoke; however, some experienced acupuncturists consider that its clinical efficacy may not be equal to that of conventional moxibustion. In the present study, a special device removing the moxa smoke will not be used in the conventional moxibustion group but only in the smoke-free group, and the same kind of moxa sticks will be chosen in these two groups to ensure that other conditions except for the moxa smoke reach consensus. The study aims to explore the influence on effectiveness of removing moxa smoke in the process of moxibustion. The device to remove the moxa smoke has been used in clinical practice, and our design is based on clinical application.

Because of the objective of this trial to clarify whether removing moxa smoke may be interfering with the clinical efficacy of conventional moxibustion, and the difficulty of using the double-blind methodology in acupuncture and moxibustion, we designed a single-blind study; therefore, it is not necessary to set up a wait-list group. The treatment acupoints and intervention period are based on some positive result studies and clinical experience in order to ensure their effectiveness [11–13, 15].

The design and methodological rigor of this trial will allow for collection of high-quality data to compare the effectiveness of conventional moxibustion and smoke-free moxibustion for patients with KOA. Thus, the trial will contribute to providing a selection of moxibustion in practice, as well as promote the clinical application of moxibustion therapy.

